3.2 Study site

Tanintharyi Division lies at the southern end of Myanmar. A narrow strip of coast between Thailand on the east and the Andaman Sea on the west, Tanintharyi extends south for c.400 mi (650 km) from Mon State to the Isthmus of Kra and includes many offshore. The area of the Division is 16,735 square miles. Out of about 1,000 islands along Myanmar's coastline over 800 are in Tanintharyi coast. Myeik is the Capital of Tanintharyi Division with three districts -- Dawei, Myeik and Kawthoung -- formed with ten Townships and 317 Wards and 328Village Tracts and the population is about 917,628. Evergreen forests thrive in the region as it is located in the tropical climate zone with torrential rains. As the land is mountainous, it is a thinly populated area. Majority of the residents of the Division live along the coastal plains and river valleys. Kawthaung District has high malaria mortality and morbidity, also a high risk area that was selected to study. Kamaukkyi Station hospital, Kawthaung, in Tanintharyi Division has been selected for the study where the falciparum malaria patients will be hospitalized for 7 days and follow-up activities will be done.

3.3 Study population

The population will consist of patients with uncomplicated *P. falciparum* malaria attending the study health clinic who are aged > 18 years. All adult patients will sign an informed consent form for participation. Patients will be hospitalized for the 7 first days.

3.4 Timing and duration of study

The study will be conducted during the malaria transmission season, from October 2010 to September 2011.

3.5 Inclusion criteria

- age > 18 years;
- mono-infection with *P. falciparum* detected by microscopy;
- parasitaemia of 10 000-100 000/µl asexual forms;
- presence of axillary ≥ 37.5 °C or oral or history of fever during the past 24 h;
- ability to swallow oral medication;
- ability and willingness to comply with the study protocol for the duration of the study and to comply with the study visit schedule; and

3.6 Exclusion criteria

- presence of signs of severe falciparum malaria according to the definitions of WHO (Appendix 1);
- mixed or mono-infection with another Plasmodium species detected by microscopy;
- presence of severe malnutrition (defined as a child whose growth standard is below –3 z-score, has symmetrical oedema involving at least the feet or has a mid-upper arm circumference < 110 mm);
- presence of febrile conditions due to diseases other than malaria (e.g. acute lower respiratory tract infection, severe diarrhoea with dehydration) or other known underlying chronic or severe diseases (e.g. cardiac, renal and hepatic diseases, HIV/AIDS);
- regular medication, which may interfere with antimalarial pharmacokinetics;
- history of hypersensitivity reactions or contraindications to any of the medicine(s) being tested or used as alternative treatment(s); and
- a positive pregnancy test or breastfeeding (include this criterion only if adults are included);
- unable to or unwilling to take a pregnancy test or contraceptives (for women of child-bearing age);
- previous antimalarial drug intake in the past 48 hours;
- patients presenting with spenectomy.

3.7 Loss to follow-up

Loss to follow-up occurs when, despite all reasonable efforts, an enrolled patient does not attend the scheduled visits and cannot be found. No treatment outcome will be assigned to these patients. Every effort must be made to schedule a follow-up visit for patients who fail to return to the study site, especially during but also after administration of the study drug. These patients will be classified as lost to follow-up and censored or excluded from the analysis. Patients who are lost to follow-up but who subsequently return to the study site before day 28 will not be turned away and will be encouraged to return for check-up visits. The principal investigator will decide whether the patient is to be definitely classified as lost to follow-up on the basis of his or her history or is to be maintained for the analysis.

3.8 Patient discontinuation or protocol violation

Study patients who meet any of the following criteria will be classified as withdrawn.

- withdrawal of consent. A patient may withdraw consent at any time, without prejudice for further follow-up or treatment at the study site.
- failure to complete treatment, due to:
- persistent vomiting of the treatment. A patient who vomits the study medication twice will be withdrawn from the study and given rescue treatment.
- failure to attend the scheduled visits during the first 3 days; or
- serious adverse events necessitating termination of treatment before the full course is completed. A patient can be discontinued from the study if the principal investigator decides so due to an adverse event of adequate nature or intensity. In this case, information on the adverse event and symptomatic treatment given must be recorded on a case report form. If the adverse event is serious, the principal investigator must notify the sponsor or its designee immediately and follow the reporting procedures described in section 5.3.
- enrolment violation:
- severe malaria on day 0; or
- erroneous inclusion of a patient who does not meet the inclusion criteria.
- voluntary protocol violation: self- or third-party administration of antimalarial drug (or antibiotics with antimalarial activity) (Appendix 2);
- involuntary protocol violation:
- occurrence during follow-up of concomitant disease that would interfere with a clear classification of the treatment outcome;
- detection of mono-infection with another malaria species during follow-up; or
- misclassification of a patient due to a laboratory error (parasitaemia), leading to administration of rescue treatment.

Patients who are withdrawn will nevertheless be followed up until recovery or the end of follow-up, if possible; however, no treatment outcome will be assigned to these patients, and they will be censored or excluded from the analysis. The reasons for discontinuation or protocol violation will be recorded on the case report form.

4. Treatment

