Background: The artemisinin resistance is not just on the Thai-Cambodia border, but may have extended to or emerged on the Thai-Myanmar, China-Myanmar and Cambodia-Viet Nam borders, confirmatory artemisinin monotherapy in vivo studies and molecular fingerprinting of parasite genomes to track artemisinin resistance (gene flow) moving around the region is even more important now. Of the data presented from these countries, the slow parasite clearance time (PCT) following treatment with artemisinin derivatives was of greatest concern. With combination therapy, artesunate usually provides the initial rapid decrease of PCT, with 95% of patients clearing peripheral parasitaemia within 48 hours, hence if the PCT is slow despite the drug being in the blood at adequate levels, this could provide evidence that it is failing.

Objective: To assess the efficacy artesunate 4 mg/day over 7 days for the treatment of uncomplicated *Plasmodium falciparum* malaria in Kawthaung (Tanintharyi Division) in Myanmar.

Methods: An antimalarial drug efficacy trial will be conducted in Kawthaung (Tanintharyi Division), Mzanmar. The participants will be febrile people > 18 years with confirmed uncomplicated *P. falciparum* infection. Patients will be treated with artesunate 28 mg/kg over 7 days. Clinical and parasitological parameters will be monitored over a 28-day follow-up period to evaluate drug efficacy. The study will be conducted from October 2010 to September 2010. The results of this study will be used to assist the Ministry of Health of Myanmar in assessing the current national treatment guidelines for uncomplicated *P. falciparum* malaria and mapping the extent of artesunate resistance.

1. Background

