4.1 Antimalarial treatment

The patients will be received artesunate 50 mg per tablet (Guilin Pharmaceutical Company, PRC) 4mg/kg/day for 7 days. Each dose administration will be observed and recorded. The correct drug dosage will be determined from the dosing chart (Appendix 3).

All doses of medicine will be administered under the supervision of a qualified member of the staff designated by the principal investigator. The study patients will be observed for 30 min after medicine administration for adverse reactions or vomiting. Any patient who vomits during this observation period will be re-treated with the same dose of medicine and observed for an additional 30 min. If the patient vomits again, he or she will be withdrawn and offered rescue therapy.

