Appendix 6. Schedule of follow-up activities

|  | Day | | | | | | | | | |
| --- | --- | --- | --- | --- | --- | --- | --- | --- | --- | --- |
| 0 | 1 | 2 | 3 | 7 | 14 | 21 | 28 | Any other |  |
| **Procedure** |  |  |  |  |  |  |  |  |  |  |
| Clinical assessment | X | X | X | X | X | X | X | X | (X) |  |
| Temperature | X | X | X | X | X | X | X | X | (X) |  |
| Blood slide for parasite count | X |  | X | X | X | X | X | X | (X) |  |
| Urine sample | (X) |  |  |  |  |  |  |  |  |  |
| Blood for:  genotyping  molecular markers  antimalarial blood concentration | X  X  11 X | X |  |  | X | X | X | X | X |  |
| Treatment |  |  |  |  |  |  |  |  |  |  |
| Medicine to be tested from day 0 to day 6 included | X | X | X | X |  |  |  |  |  |  |
| Rescue treatment |  | (X) | (X) | (X) | (X) | (X) | (X) | (X) | (X) |  |

Parentheses denote conditional or optional activities. For example, treatment would be given on days 1 and 2 only for 3-day dosing. On day 1, the patient should be examined for parasitaemia if he or she has any danger signs. Rescue treatment could be given on any day, provided that the patient meets the criteria for treatment failure. Extra days are any days other than regularly scheduled follow-up days when the patient returns to the facility because of recurrence of symptoms. On extra days, blood slides may be taken routinely or at the request of the clinical staff.

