|  |  |  | | Yes  No |  |
|  |  |  | | Yes  No |  |

| **Case report form: follow-up day 7** | | | | | |
| --- | --- | --- | --- | --- | --- |
| Study number: | | | | | |
| Patient identity number: | | | | | |
| Date of visit (dd-mmm-yyyy): | | | | | |
| **Clinical status** | | | | | |
| Presence of danger signs or signs of severe or complicated malaria?  Yes  No | | | | | |
| History of fever within previous 24 h?  Yes  No | | | | | |
| Temperature:       ºC  Axillary  Tympanic  Rectal  Oral | | | | | |
| **Thick blood smears for estimation of *P. falciparum* parasite counts** | | | | | |
| Average number of asexual *P. falciparum* parasites/l: | | | | | |
| Presence of *P. falciparum* gametocytes?  Yes  No | | | | | |
| Were species other than *P. falciparum* present?  Yes  No | | | | | |
| If yes, which species?  *P. vivax*  *P. ovale*  *P. malariae* | | | | | |
| Has a blood sample for PCR been collected?  Yes  No | | | | | |
| **Adverse events** | | | | | |
| Presence of an adverse event?  Yes  No | | | | | |
| If yes, name the adverse event: | | | | | |
| Is it a serious adverse event?  Yes  No. If yes, inform the sponsor. | | | | | |
| **Medication administration** | | | | | |
| Name(s) of antimalarial drug(s) | | Time of dose (hh:min) | Number of tablets | Did the patient vomit? | Time of vomiting (hh:min) |
|  | |  |  | Yes  No |  |
|  | |  |  | Yes  No |  |
| Name(s) of other medicine(s) |  | | | | |
|  | |  |  | Yes  No |  |
|  | |  |  | Yes  No |  |

| **Case report form: follow-up day 14** | | | | |
| --- | --- | --- | --- | --- |
| Study number: | | | | |
| Patient identity number: | | | | |
| Date of visit (dd-mmm-yyyy): | | | | |
| **Clinical status** | | | | |
| Presence of danger signs or signs of severe or complicated malaria?  Yes  No | | | | |
| History of fever within previous 24 h?  Yes  No | | | | |
| Temperature:       ºC  Axillary  Tympanic  Rectal  Oral | | | | |
| **Thick blood smears for estimation of *P. falciparum* parasite counts** | | | | |
| Average number of asexual *P. falciparum* parasites/l: | | | | |
| Presence of *P. falciparum* gametocytes?  Yes  No | | | | |
| Were species other than *P. falciparum* present?  Yes  No | | | | |
| If yes, which species?  *P. vivax*  *P. ovale*  *P. malariae* | | | | |
| Has a blood sample for PCR been collected?  Yes  No | | | | |
| **Adverse events** | | | | |
| Presence of an adverse event?  Yes  No | | | | |
| If yes, name the adverse event: | | | | |

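### The non-attendance criterion for incomplete treatment stops at 3 days although dosing runs for 7, so a patient who misses later doses and is seen again can count as fully treated at day 28

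*Protocol*

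**What the plan says.** Section 4.1 gives artesunate at "4mg/kg/day for 7 days". The abstract gives the total: "Patients will be treated with artesunate 28 mg/kg over 7 days". The treatment row of the Appendix 6 grid is labelled "Medicine to be tested from day 0 to day 6 included". Section 3.1, by contrast, ties the end of treatment to parasite clearance.

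Section 3.8 lists three causes under failure to complete treatment:

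- Vomiting: "A patient who vomits the study medication twice will be withdrawn from the study", with no day limit.
- Absence: "failure to attend the scheduled visits during the first 3 days".
- Harm: "serious adverse events necessitating termination of treatment before the full course is completed". The text adds: "A patient can be discontinued from the study if the principal investigator decides so due to an adverse event of adequate nature or intensity".

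Consent may also be withdrawn at any time. The protocol violations in 3.8 concern enrolment errors, other antimalarials, concomitant disease, another malaria species and laboratory error.

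Section 8.2 takes its withdrawals from 3.8 and adds only PCR-based ones. Appendix 9 excludes withdrawals, violations and losses to follow-up from the per-protocol proportion and censors them in the Kaplan-Meier analysis.

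**The concern.** Of the three causes of incomplete treatment, only absence has a time limit, and the limit ends before dosing does. It suits a 3-day course. The note under the Appendix 6 grid still uses 3-day dosing as its example, so the limit may be carried over from a general text, though the protocol does not say so.

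Day-28 efficacy is part of the primary objective in section 2, and the results are meant to show whether artemisinin resistance is present. If a patient who missed late doses recrudesces, the failure is charged to the full 7-day course. If that patient is cured, the full course is credited with a success it did not earn. Either way, the day-28 estimate no longer describes only the regimen it is reported for.

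Record-keeping has a related weakness. The Appendix 6 grid has no columns for days 4, 5 or 6, and its treatment marks stand under days 0 to 3 only. In Appendix 7 the dated pages go from day 3 straight to "Case report form: follow-up day 7". Missed late doses could therefore be hard to identify at analysis.

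**Working it through.** **1. Total dose.** 7 daily doses × 4 mg/kg = 28 mg/kg, which reproduces the abstract's figure. The intended course is seven doses on days 0 to 6.

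**2. Doses outside the absence clause.**

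- If the limit runs through day 3, doses on days 0, 1, 2 and 3 are covered and 7 − 4 = 3 are not: 3 × 4 = 12 of 28 mg/kg, 12/28 = 43%.
- If it means days 0 to 2, 7 − 3 = 4 are not covered: 4 × 4 = 16 of 28 mg/kg, 16/28 = 57%.

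These figures describe the reach of one clause. They do not measure bias.

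**3. Whether another rule catches the patient.** Take a patient who leaves on day 4, misses the remaining doses, does not withdraw consent and attends on day 7 or 14.

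- 3.8, vomiting or serious adverse event: not met.
- 3.8, absence: not met, because the absence falls after the limit. The grid also schedules no visit on days 4 to 6, so a longer limit worded in visits would still miss it.
- 3.8, protocol violations: missed doses are not listed.
- 3.7, loss to follow-up: requires that the patient cannot be found. For a lost patient who returns before day 28, the principal investigator decides, and no dosing criterion is given.
- 8.2 and Appendix 9: no category for missed doses.

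Such a patient can therefore be assigned an outcome and counted in both day-28 analyses.

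**4. Weight of one patient.** Section 8.1 gives a minimum of 40 and a target of 50. One failure is 1/50 = 2.0 points or 1/40 = 2.5 points. (The 40 does not follow from 8.1's own inputs: 1.96² × 0.15 × 0.85 / 0.10² = 48.98, so 49. That is a separate matter; 40 serves here only as a denominator.)

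**5. Illustration.** Assume 40 evaluable patients, 5% failure among the fully treated, *k* patients with missed late doses kept in, and failure risk *r* among them. These values are assumptions; the documents give none of them except the 40.

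Estimate = [0.05 × (40 − *k*) + *r* × *k*] / 40. If the *k* patients are excluded, the estimate is 5.0%.

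| *k* | *r* | Estimate | Shift (points) |
|---|---|---|---|
| 1 | 25% | (1.95 + 0.25)/40 = 5.5% | +0.5 |
| 1 | 100% | (1.95 + 1.00)/40 = 7.4% | +2.4 |
| 2 | 50% | (1.90 + 1.00)/40 = 7.3% | +2.3 |
| 4 | 0% | (1.80 + 0.00)/40 = 4.5% | −0.5 |
| 4 | 50% | (1.80 + 2.00)/40 = 9.5% | +4.5 |
| 4 | 100% | (1.80 + 4.00)/40 = 14.5% | +9.5 |

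With *k* = 0 there is no shift.

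**6. Endpoints touched.** Doses missed after day 3 cannot alter day-3 positivity or the 48-hour reduction. Parasite clearance time is touched only in patients still parasitaemic after day 3. The exposure is in the day-28 success and failure results.

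**The case against.** The strongest reply is that the gap will rarely matter. Sections 3.2 and 3.3 keep patients in hospital for 7 days, 4.1 has every dose supervised and recorded, and 6.2 requires efforts to find defaulters so that they complete treatment. This stands: cases should be few, possibly none.

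A reader might infer that the whole incomplete-treatment rule ends at day 3, or that every patient who misses late doses stays in. The text does not support that. The vomiting and serious-adverse-event grounds run through the course, consent can be withdrawn at any time, the investigator may discontinue for an adverse event, a patient who cannot be found is lost to follow-up, and 3.7 lets the investigator classify some who return as lost.

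A reader might also infer that doses on days 4 to 6 have no form at all. That is not so. Appendix 7 has a page for any other day with a medication table, and Appendix 3 names a Dose Administration Form. What remains is that the any-other-day page has a single smear entry against the 12-hourly sampling in 5.2.4, Appendix 6 describes extra days as returns for symptoms, and the Dose Administration Form is not among the forms in Appendix 7.

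It can be argued that failure to complete treatment stands as a ground by itself. But 3.8 ties it to three listed causes, so a fourth has to be read in.

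Finally, a detailed per-protocol definition may sit in a statistical analysis plan. The point here is not its absence. Section 3.8 states a rule, 8.2 relies on it, and the rule stops before dosing does.

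**Conclusion.** The point holds in a narrow form. Followed as written, 3.8 can leave an incompletely treated patient in the day-28 per-protocol and Kaplan-Meier results when late doses are missed through absence, early departure or refusal and the patient is seen again. Whether this happens also depends on the discretion in 3.7 if the patient was first regarded as lost.

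The size is 2 to 2.5 points on the failure proportion per affected patient who fails. The total depends on a number of cases that the documents do not give; under the assumptions above, up to four cases shift the estimate by between −0.5 and +9.5 points. With inpatient supervised dosing the low end is more plausible.

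A reader might go further and conclude that the trial's early resistance signal is compromised. The documents do not support this: the background names day-3 positivity as the early-warning measure and 8.1 sizes the study on it, and doses missed after day 3 cannot change it.

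**What to change.** Reconcile 3.8 with the dosing period in 4.1 and Appendix 6, and with 3.1, so that a complete course has one definition.

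For the analysis only, state in 3.8 or 8.2 that a patient with doses missed at any time through day 6 is classified as incompletely treated: excluded from the per-protocol day-28 proportion, censored in the Kaplan-Meier analysis as Appendix 9 does for withdrawals and violations, and kept for the early clearance endpoints. Word it by doses rather than visits.

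Add day 4, 5 and 6 columns to Appendix 6, and matching dose and 12-hourly smear fields to Appendix 7.

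This should remain an analysis classification. Section 9.4 attaches treatment arrangements to withdrawal before the full course, and no change to clinical withdrawal or treatment is proposed.

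The cost is a sentence or two and three short form pages. A few patients may move from evaluable to excluded or censored at day 28, a small loss of precision.

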4.1 Antimalarial treatment

The patients will be received artesunate 50 mg per tablet (Guilin Pharmaceutical Company, PRC) 4mg/kg/day for 7 days. Each dose administration will be observed and recorded. The correct drug dosage will be determined from the dosing chart (Appendix 3).

All doses of medicine will be administered under the supervision of a qualified member of the staff designated by the principal investigator. The study patients will be observed for 30 min after medicine administration for adverse reactions or vomiting. Any patient who vomits during this observation period will be re-treated with the same dose of medicine and observed for an additional 30 min. If the patient vomits again, he or she will be withdrawn and offered rescue therapy.

4.2 Concomitant treatment and medication that should not be used

Fever over 38 °C can be treated with paracetamol or acetaminophen.

During follow-up, if infections other than malaria require the administration of medicines with antimalarial activity, the patient will be withdrawn from the study. Patients given tetracycline as an eye ointment will not be excluded (Appendix 2). Patients will be withdrawn from the study in the case of self-medication or if an antimalarial drug or an antibiotic with antimalarial activity is administered by a third party.

Adverse events requiring treatment can be treated according to local practice. If there is a clinical indication for any additional medication during the course of the study, including medication given to treat an adverse event related to the study medicine, the name of the medicine, the dosage and the date and time of administration must be recorded on the case report form.

The use of herbal remedies during the study should be avoided, and participants should be encouraged to return to the study site for treatment if they feel unwell. If any herbal remedies are taken during the study, this should be captured on the case report form, under ‘study medication administration’.

4.3 Rescue treatment

If a patient meets one of the criteria for therapeutic failure, ETF and LTF cases, he/she will receive the other artemether-lumefantrine. If the patient is reinfected with another malaria species (*P. vivax, P. malariae or P. ovale*) he/she will receive chloroquine total dose of 25mg base/kg over three days, followed by primaquine 0.25mg/kg/day for 14 days (except for *P. malariae*) according to the current national recommendations.

If the patient vomits the treatment twice, he/she will receive parenteral therapy with artemether IM (80mg/ amp) injection 160mg at 0hrs and l2th hours, and 80 mg at 24th and 48th hours (total = 480mg) plus oral mefloquine (500mg) x 2 doses at 48th and 54th hours and be withdrawn from the study.

With any sign of severe malaria, the study patient will be treated with quinine injection 8 mg/kg of quinine base every 8 hours. Quinine will be given 3 time a day until the patient can reliably take oral medication. The patient will then continue on oral quinine (3x8 mg/kg/day) until they have completed seven days treatment. A seven days course of doxycycline (3 mg/kg/day) will be given also to patients as well as relevant supportive treatments.

5. Evaluation criteria

The study end-point is the classification assigned to a patient. Valid study end-points include: the number of patients parasite positive at day 3, PCT, parasite reduction rate (slope of the log-linear parasite clearance curve), the parasite reduction rate at 48 hours, treatment failure, completion of the follow-up period without treatment failure, loss to follow-up, withdrawal from study, and protocol violation. At all times, the well-being of the patient will take priority over his or her continuation in the study. Secondary end-point is the pharmacokinetic profile of the patients.

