5.1 Efficacy and safety evaluation

### 5.1.1 Classification of treatment outcomes

Artesunate should produce parasite reduction ratios of approximately 10,000/cycle, which result in parasite clearance times, which are usually less than 48 hours. This is a descriptive study; its purpose will be a detailed analysis of how the group responds.

Treatment outcomes will be classified on the basis of an assessment of the parasitological and clinical outcome of antimalarial treatment according to the latest WHO guidelines.[[1]](#footnote-2) Thus, all patients will be classified as having early treatment failure, late clinical failure, late parasitological failure or an adequate clinical and parasitological response, as defined in Appendix 4.

As parasitological cure is the goal of antimalarial therapy, all study patients who show treatment failure will be given rescue treatment. Follow-up will continue until recovery. The results from these patients do not need to be recorded systematically for the purpose of the surveillance study.

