Appendix 4. Classification of treatment outcomes[[5]](#footnote-6)

**Early treatment failure**

- danger signs or severe malaria on day 1, 2 or 3 in the presence of parasitaemia;
- parasitaemia on day 2 higher than on day 0, irrespective of axillary temperature;
- parasitaemia on day 3 with axillary temperature ≥ 37.5 ºC;
- parasitaemia on day 3 ≥ 25% of count on day 0.

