**Late treatment failure**

**Late clinical failure**

- danger signs or severe malaria in the presence of parasitaemia on any day between day 4 and day 28 (day 42) in patients who did not previously meet any of the criteria of early treatment failure;
- presence of parasitaemia on any day between day 4 and day 28 with axillary temperature
  ≥ 37.5 ºC (or history of fever) in patients who did not previously meet any of the criteria of early treatment failure

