**Day 1**

- clinical assessment; referral in cases of severe malaria or danger signs;
- measurement of axillary temperature;
- parasitological assessment in cases of severe malaria or danger signs;
- treatment, second dose or alternative treatment in case of early treatment failure.

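### Section 4.3 places a parasitaemic patient with severe malaria under two rescue rules that name different drugs, and the protocol states no precedence

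*Protocol*

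**What the plan says.** Section 4.3 of the protocol sets out rescue treatment by situation. Two of its rules matter here.

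- **Failure rule:** "If a patient meets one of the criteria for therapeutic failure, ETF and LTF cases, he/she will receive the other artemether-lumefantrine". It covers early and late treatment failures alike and makes no exception.
- **Severe-malaria rule:** "With any sign of severe malaria, the study patient will be treated with quinine injection 8 mg/kg of quinine base every 8 hours". Oral quinine follows to complete seven days, with a seven-day course of doxycycline. This rule has no exception either.

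Appendix 4 defines failure. The first criterion for early treatment failure is "danger signs or severe malaria on day 1, 2 or 3 in the presence of parasitaemia". The first criterion for late clinical failure is "danger signs or severe malaria in the presence of parasitaemia on any day between day 4 and day 28", in patients who were not already early failures.

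Section 5.1.1 adds that "all study patients who show treatment failure will be given rescue treatment". The visit lists in Appendix 6 call for "clinical assessment; referral in cases of severe malaria or danger signs" and, for the same visits, for alternative treatment if the patient is a failure.

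**The concern.** The failure rule and the severe-malaria rule read as if they dealt with different patients. They do not, because Appendix 4 counts severe malaria with parasitaemia as a treatment failure. Such a patient is assigned artemether-lumefantrine by one sentence and injectable quinine with doxycycline by another sentence of the same section.

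This concerns the sickest patients in a study of artesunate monotherapy that is looking for resistance. Two members of staff could each follow the protocol to the letter and give the same patient different drugs.

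**Working it through.** The protocol gives no figure on this point, so there is nothing to recompute. The check sets the triggers side by side.

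**Step 1: triggers.** The failure rule applies when any Appendix 4 failure criterion is met. The severe-malaria rule applies when a study patient has any sign of severe malaria; Appendix 1 lists those signs.

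**Step 2: overlap.**

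| Patient | Failure rule | Severe-malaria rule |
| --- | --- | --- |
| Severe malaria with parasitaemia, days 1 to 3 | Yes (early treatment failure) | Yes |
| Severe malaria with parasitaemia, days 4 to 28 | Yes (late clinical failure, if not already an early failure) | Yes |
| Danger signs with parasitaemia, days 1 to 28, no Appendix 1 sign | Yes | No |
| Failure by parasite count or fever only | Yes | No |
| Severe malaria without parasitaemia | Not by the severe-malaria criterion | Yes |

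Severe malaria on day 0 lies outside the overlap: section 3.8 treats it as an enrolment violation, and the patient is withdrawn with no outcome assigned. Only the first two rows meet both triggers, but every patient in those rows does so by definition.

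**Step 3: search for a precedence rule.**
- Section 4.3 lists its situations one after another and does not rank them.
- Section 5.1.1 requires rescue for every failure and does not set severe cases apart.
- The notes to Appendix 6 make rescue conditional on meeting the failure criteria, which leads back to the failure rule.
- The Appendix 6 visit lists call for referral in severe cases but name no drug.

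None of these settles which sentence of section 4.3 governs.

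**Step 4: effect on the results.** Appendix 9 counts early treatment failure, and late clinical failure before day 7, as failures. From day 7 the PCR-corrected outcome depends on genotyping. In neither case does the rescue drug enter, and section 5.1.1 does not require results after rescue to be recorded systematically. The classification and the day-28 estimate are the same under either rule.

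**The case against.** The best reply is that the text nearly resolves itself. The severe-malaria sentence is the more specific one. Severe malaria at entry is an exclusion or an enrolment violation, and later severe malaria with parasitaemia always meets Appendix 4. Unless the quinine sentence displaces the artemether-lumefantrine sentence, it would apply to almost no evaluable patient. On this view there is a general rule with an unstated exception, and the fault is one of drafting.

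That reading is plausible, but it is not written. The failure rule covers all early and late failures, and that class expressly includes severe malaria. An instruction for acute care should not rest on inference.

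The objection does limit the point. A reader might infer more than the document supports in five ways.

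- **Different routes.** One might say that the rules set an oral drug against an injected one. Section 4.3 gives no route for artemether-lumefantrine, and the conflict is between the named drugs.
- **A third conflicting instruction in Appendix 6.** Referral names no drug and is listed with alternative treatment for the same visits, so it does not contradict either rule.
- **Double assignment for danger signs.** The protocol does not define danger signs, and the quinine sentence does not mention them. A patient with danger signs but no Appendix 1 sign falls under the failure rule alone. Whether that is intended should be stated, but it is not a contradiction.
- **An expected count.** The one early failure reported in the background was identified by parasite count under combination therapy. It gives no rate of severe malaria for this study.
- **Biased efficacy.** The classification does not depend on which rescue drug is given.

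**Conclusion.** The point holds for severe malaria with parasitaemia on days 1 to 28: section 4.3 and Appendix 4 together assign two different rescue regimens, and no precedence is stated. This is a conflict between two stated rules and not merely a missing detail.

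The affected group is probably a small part of the 50 patients targeted, but the document gives no basis for a number. No efficacy result changes. The case for correction rests on patient safety and uniform conduct, and on how little the correction costs. The conclusion assumes that the two sentences mean what they say. If the sponsor intended one to override the other, the fault is that the protocol does not say so. No view is taken on which treatment is right.

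**What to change.** Reconcile the two rescue sentences in section 4.3 with Appendix 4. Either word the triggers so that each failure falls under exactly one rule, or add a sentence stating which rule takes precedence when both are met.

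In the same amendment, say which rule covers danger signs that are not signs of severe malaria under Appendix 1. The new wording should be checked against that group, because narrowing the failure sentence alone could leave it under no rule. The sponsor's clinicians decide which treatment applies to whom.

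The cost is one or two sentences in a protocol amendment. No extra patients, visits or data are needed.
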